### Main Objectives

(1)In light of the above, the first objective of this study is to evaluate the prevalence of both maternal antepartum and postpartum depression and anxiety in a large sample of women attending healthcare centers in Italy.(2)The second objective, parallel to the first, is to investigate the psychosocial risks and protective factors associated with maternal antepartum and postpartum depression and anxiety.(3)The third objective, building on the first, is to evaluate the psychometric properties of both the Edinburgh Postnatal Depression Scale (Cox et al., 1987) and the Patient Health Questionnaire-9 (Kroenke et al., 2001) in detecting perinatal depression.(4)The fourth objective is to evaluate the effectiveness of a manualized psychological intervention (Milgrom et al., 1999) for both antenatal and postnatal depression in a large sample of mothers in Italy.(5)The final objective is to evaluate the influence of maternal depression and anxiety on the development of baby temperament during a period of a minimum of 12 months up to a maximum of 18 months from birth.

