#### Phase 2: Screening for Psychosocial Risks, Depression, and Anxiety

Screening is performed once during the pre- or post-partum period, depending on the characteristics of each healthcare center. All mothers complete the Psychosocial and Clinical Assessment Form (Mirabella et al., 2016), the Italian versions of both the Edinburgh Postnatal Depression Scale (EPDS) (Cox et al., 1987; Benvenuti et al., 1999) and the Patient Health Questionnaire-9 (PHQ-9) (Kroenke et al., 2001) to evaluate depressive symptoms and the Italian version of the State-Trait Anxiety Inventory (STAI) (Spielberger et al., 1983; Pedrabissi and Santinello, 1992) to evaluate anxiety.

Mothers are required to complete the psychodiagnostic evaluation within one week of the date of positive screening results.

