#### Phase 3: Psychodiagnostic Evaluation

All mothers undergo an interview with a clinical psychologist. Within the following week, in the case of clinician-generated diagnosis of perinatal depression and/or anxiety (according to the DSM-5 criteria), these mothers are further assessed using the Mini-International Neuropsychiatric Interview (MINI) Plus (Lecrubier et al., 1997; Sheehan et al., 1998) to confirm the diagnosis, the World Health Organization Quality of Life (WHOQOL) BREF (The Whoqol Group, 1998) to assess the quality of life and the Italian Questionnaires of Temperament (QUITs) (Axia, 2002) to assess the babies’ traits in temperament.

All mothers receive verbal feedback about the results of the psychodiagnostic evaluation. Depressed and/or anxious mothers are invited to participate in the intervention phase of the study. Whereas mothers with postpartum psychotic disorders, non-suicidal self-harm tendencies or suicidal ideation are sent to a psychiatric service and excluded from the study.

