### Data Analysis Plan

The prevalence of antenatal and postpartum depression and the risk of anxiety will be calculated and compared. Since previous studies have ascertained a higher risk of developing depression in the postpartum period, the antenatal period will be taken as a reference to calculate the odds ratio as a measure of the relative risk of depression between antenatal and postpartum periods, using chi-square as a test for statistical significance.

The sensitivity, specificity and predictive values of the EPDS and the PHQ-9 versus the MINI will be analyzed. Factors associated with ante- and post-partum depression and anxiety risk will be analyzed using a logistic regression model.

With regard to the effectiveness of treatment, standard descriptive statistics will be calculated for all questionnaires. Analysis of variance for repeated measurements will be performed to compare the differences between each initial score obtained with the different administered questionnaires and the scores at T1 (end of treatment), T2 (after 6 months) and T3 (after 12 months) will be evaluated. Bonferroni *post hoc* comparisons will be conducted. Treatment effect will be calculated using Cohen’s d for each of the follow-up times. The Reliable Change Index will be calculated for each time, in order to determine any significant clinical changes occurring in each individual case post treatment.

Data will be analyzed using the Statistical Package for Social Science (SPSS) for Windows version 22.0.

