### Strengths and Limitations of This Study

This study presents some strengths and limitations that should be mentioned. The main strengths are: (a) this study provides a new knowledge about the prevalence of perinatal depression and anxiety during both the trimesters of pregnancy and the first four trimesters after birth; (b) the large sample size is based on eleven recruitment centers located throughout Italy, and then it is representative of the pregnant population in Italy; and (c) all mothers were assessed for depression and anxiety through both self-report questionnaires and clinical interviews. The main limitation of the study is that it cannot monitor the timing and patterns of onset, duration, remission and recurrence of anxiety and depression during the entire perinatal period. Another limitation is that this protocol is the absence of a control group or waiting list condition.

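### EPDS and PHQ-9 accuracy is to be computed against a MINI given only to mothers already diagnosed by the clinician, which distorts the predictive values and leaves sensitivity and specificity unreliable

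*Protocol article*

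**What the plan says.** The third of the Main Objectives is to evaluate the psychometric properties of the EPDS and the PHQ-9 "in detecting perinatal depression". The Data Analysis Plan serves it with one sentence: "The sensitivity, specificity and predictive values of the EPDS and the PHQ-9 versus the MINI will be analyzed".

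Under Phase 2 both scales, with the STAI, are completed by all mothers. Under Phase 3 all mothers are interviewed by a clinical psychologist, and the MINI-Plus then follows only on a stated condition: "in the case of clinician-generated diagnosis of perinatal depression and/or anxiety (according to the DSM-5 criteria". Its purpose is given as "to confirm the diagnosis". The MINI-Plus section adds that only the depressive disorders module is used.

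On who is interviewed, Strengths and Limitations agrees with Phase 3: "all mothers were assessed for depression and anxiety through both self-report questionnaires and clinical interviews". Phase 2 words it differently: "Mothers are required to complete the psychodiagnostic evaluation within one week of the date of positive screening results".

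The MINI appears again in Phase 5, but there it re-evaluates patients after the intervention.

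**The concern.** An accuracy table needs the reference result in mothers with and without the condition, whatever the clinician thought of them. Here the reference is applied only after a positive clinical judgement. A depressed mother whom the clinician misses never enters the table. Nor does the large majority who are well. MINI-negative mothers can be only two kinds: those the clinician wrongly diagnosed as depressed, and those diagnosed with anxiety alone, who are negative because only the depression module is used.

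The article's Background notes that healthcare providers have little training in choosing a screening tool and cut-off. Accuracy figures from a selected subset could mislead exactly that choice, above all on how far a negative screen can be trusted.

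**Working it through.** **Inputs from the article.** EPDS sensitivity 0.556 and specificity 0.989 at a cut-off of 12 or more (EPDS section); 500 mothers and 10–15% prevalence (Sample Size). The article gives no target for the accuracy analysis, so there is no planned figure to reproduce. As a check on the inputs, the quoted PPV of 90.9% implies prior odds of (0.909/0.091) × (0.011/0.556) = 0.198, a prevalence of 16.5%, close to the planning range.

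**Assumptions.** The article gives no clinician detection rates. I write v for the probability that the clinician diagnoses the mother, so that she gets the MINI, in four groups: EPDS-positive cases, EPDS-negative cases, EPDS-positive non-cases, EPDS-negative non-cases.

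**Full table at 15%.** 75 cases: TP = 75 × 0.556 = 41.7, FN = 33.3. 425 non-cases: FP = 425 × 0.011 = 4.68, TN = 420.32. True PPV = 41.7/46.38 = 0.899; true NPV = 420.32/453.62 = 0.927. At 10% the same steps give 0.849 and 0.952.

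**Table as planned.** Each cell is multiplied by its v. Where two values are shown they are for 10% and 15% prevalence.

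| v (four groups) | MINI done | Sens. | Spec. | PPV | NPV |
|---|---|---|---|---|---|
| .90/.90/.05/.05 | 68; 89 | 0.556 | 0.989 | 0.990; 0.994 | 0.527; 0.412 |
| .90/.90/.10/.10 | 90; 110 | 0.556 | 0.989 | 0.981; 0.988 | 0.690; 0.584 |
| .95/.60/.50/.05 | 65; 83 | 0.665 | 0.900 | 0.914; 0.944 | 0.626; 0.513 |
| .95/.60/.50/.10 | 87; 104 | 0.665 | 0.947 | 0.914; 0.944 | 0.770; 0.678 |
| .98/.60/.50/.02 | 52; 72 | 0.672 | 0.782 | 0.917; 0.946 | 0.401; 0.296 |
| 1/1/0/0 | 50; 75 | 0.556 | none | 1.00 | 0 |

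Example, fifth row at 15%: cells 40.9, 20.0, 2.3 and 8.4. Sensitivity 40.9/60.9 = 0.67; specificity 8.4/10.7 = 0.78; PPV 40.9/43.2 = 0.95; NPV 8.4/28.4 = 0.30.

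**Anxiety-only mothers.** The first row ignores them. Taking anxiety at 10–24% (Background) and assuming 40% of those women are also depressed, 500 × 0.10 × 0.6 = 30 to 500 × 0.24 × 0.6 = 72 mothers have anxiety alone. With 90% of them diagnosed plus 5% of other non-cases, verified non-cases at 15% number 27 + 0.05 × 395 = 46.8 to 64.8 + 0.05 × 353 = 82.5. NPV becomes 46.2/(46.2 + 30.0) = 0.61 to 81.5/(81.5 + 30.0) = 0.73. At 10% prevalence it is 0.70 to 0.81. All remain well below 0.93–0.95.

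**What does not depend on the chosen rates.** Planned NPV = TN·v₄/(TN·v₄ + FN·v₂). This is below the true NPV whenever v₂ > v₄, that is, whenever the clinician is likelier to diagnose a depressed mother than a non-depressed one among EPDS-negatives. By the same argument PPV is too high whenever v₁ > v₃. Any useful interview meets both conditions. Sensitivity is biased only if v₁ differs from v₂, and specificity only if v₃ differs from v₄.

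**The case against.** Much can be said against a stronger reading.

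- A reader might infer that all four measures must be wrong. The first two rows show otherwise: sensitivity and specificity are unbiased if diagnosis is independent of the scale score given true status. I think independence unlikely, since interview and scales ask about the same symptoms, but the correlation is assumed.
- A reader might take Phase 2 to mean sensitivity of 100% and specificity of 0% by construction. That needs verification triggered by the EPDS alone. The screen comprises the EPDS, PHQ-9 and STAI, and no text ties a positive result to one scale. The Phase 2 sentence sets a time limit and does not say that only screen-positive mothers are interviewed; two other sections say all are.
- A reader might say that true negatives are almost absent, about 21 of 425 non-cases (5%). That leaves out anxiety-only mothers, who raise the count to about 47–82. They are still a selected group, and the article itself notes that state anxiety correlates strongly with the EPDS.
- A specificity of 0.78 is not robust: moving v₄ from 0.02 to 0.05 in the fifth row gives 0.90.
- PPV may look safe, but among MINI-verified mothers it is inflated too.
- The third objective is wider than accuracy. Reliability can be assessed in all screened mothers and is unaffected, and diagnostic accuracy is not listed among the Study Outcomes.

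A statistical analysis plan, not shown here, might name another reference or a correction. But this is not detail left for later: the article names the MINI as comparator and states a rule for giving it that cannot support the comparison.

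**Conclusion.** The analysis as written does not answer the accuracy part of the third objective. The distortion of the predictive values is firm in direction: NPV is about 0.30 to 0.81 against 0.93 to 0.95, and PPV 0.91 to 0.99 against 0.85 to 0.90, leaving aside the limiting case of a clinician who is never wrong (NPV 0, PPV 1). The sizes rest on assumed clinician rates; the direction needs only an interview better than chance. Specificity rests on clinician false positives and anxiety-only mothers, and cannot be estimated if the MINI confirms every diagnosis. Sensitivity is probably too high, about 0.67 against 0.556 under the correlated rates assumed. The figures are for the EPDS; the PHQ-9 is verified by the same rule, so the same argument applies.

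**What to change.** In the Data Analysis Plan, name the DSM-5 clinical interview as the reference standard for sensitivity, specificity, PPV and NPV of both scales in all screened mothers. Count a diagnosis of depression only, not anxiety alone. Use the MINI only to report how often it confirms the clinician's depression diagnosis among those who receive it.

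Reconcile Phase 2 with Phase 3 and with Strengths and Limitations on who is interviewed. If only screen-positive mothers are, drop sensitivity, specificity and NPV, and report PPV against the interview among all mothers positive on the scale in question.

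This is a wording change and needs no new data if all mothers are interviewed as stated. The cost is an unstructured reference with its own errors, so results should be labelled as accuracy against clinician diagnosis. State whether interviewers see the scale scores. If they do, some bias remains: with the fifth-row rates at 15%, sensitivity is (40.9 + 2.3)/71.6 = 0.60 against 0.556, and NPV 425.2/453.6 = 0.94 against 0.927. Clinician errors unrelated to the scale pull the other way: if all first-row diagnoses were of depression, sensitivity would be 37.8/88.8 = 0.43 and NPV 402.6/453.6 = 0.89. Both NPVs are far nearer the truth than those in the table above, but the sensitivity needs this limitation stated beside it. Giving the MINI to a random sample of undiagnosed mothers, with weighting, would avoid the problem at the price of new data collection.

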### Hypotheses

(1)On the basis of the current literature (Underwood et al., 2016; Okagbue et al., 2017; Hahn-Holbrook et al., 2018), we expect to find a prevalence of perinatal depression within the range of 13–18%, with higher rates during pregnancy than in the first year following childbirth.(2)Based on previous research (Ghaedrahmati et al., 2017; Leach et al., 2017), we assume that the factors associated with a higher risk of perinatal depression and anxiety will include previous history of depression and anxiety, a negative attitude toward a recent previous pregnancy, high-risk pregnancy, young maternal age, limited social support, and financial problems.(3)In accordance with previous studies on screening for antenatal or postnatal depression (Yawn et al., 2009; Zhong et al., 2014; Santos et al., 2016), we expect that both the Edinburgh Postnatal Depression Scale and the Patient Health Questionnaire-9 will be reliable and valid scales for the assessment of perinatal depression.(4)Based on a prior Italian study (Mirabella et al., 2016) showing the effectiveness of Jeannette Milgrom’s (Milgrom et al., 1999) psychological intervention among women suffering from postpartum depression, we assume that intervention can be effective also with antepartum depressed women.(5)Given that the literature (Erickson et al., 2017) has offered ambiguous results on the association between prenatal maternal mental health and the development of infant temperament, we have no specific assumptions to this regard.

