#### Phase 4: Intervention

The intervention is based on the model developed by Milgrom at the Australian Parent-Infant Research Institute (PIRI) at Heidelberg Repatriation Hospital (Milgrom et al., 1999, 2011, 2015a,b; Milgrom and Gemmil, 2015) to reduce maternal prenatal and postnatal depression, anxiety and parenting difficulties. Moreover, this model provides for the simultaneous assessment of the neurobiological, psychological and social factors that contribute to developing psychological vulnerability in the perinatal period.

Milgrom developed a psychosocial and psychological treatment by adapting Cognitive-Behavioral Therapy (CBT) interventions for women suffering from depression both in pregnancy and postpartum (Milgrom et al., 1999; Milgrom and Gemmil, 2015). The effectiveness of this treatment has been assessed in both short- and long-term application, and its validity has been demonstrated and compared to pharmacological therapy using antidepressants. It has been deemed more effective than drugs in maintaining long-term results (Milgrom et al., 2015a).

The intervention consists of group-based CBT and focuses on the women’s life events and mood and on practical issues. The intervention takes place primarily in groups because the group setting allows participants to meet, compare and share their experiences, offering mutual support. However, in the event of impossibility of organizing a group of at least three participants within a few weeks of the psychodiagnostic evaluation, or where a participant is unable to take part regularly in weekly group sessions due to health or organizational reasons, each healthcare center offer the option of individual treatment. This solution allows a more flexible approach than group treatment, since the program can be adapted to the specific situation of the woman in question. In both cases, information and activity material are distributed between sessions.

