### Sample Size

Assuming 10–15% prevalence of perinatal depression as measured by EPDS (Gavin et al., 2005; Melville et al., 2010) the minimum number needed of mothers to be screened is 500.

With regard to the clinical trial on the psychological interventions for perinatal depression and anxiety, the power calculation was based on detecting an effect size of medium magnitude (*d* = 0.55) at the follow-ups on the EPDS among the patients (Cohen, 1988). We calculated that a sample size of 45 patients would result in a power of 0.95 with alpha set at 0.05. To protect against an anticipated loss to follow-up of about 30% (Mirabella et al., 2016), we planned to enroll 65 patients.

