### Quality Control

The healthcare centers enter all the data collected with the instruments during the Assessment into an Excel database, prepared by the ISS (baseline + follow-up). Once the centers have entered all the data collected, each researcher (coordinator of the healthcare centers) performs a detailed quality control assessment. After this assessment by each center, the data is sent to the Observatory of Perinatal Clinical Psychology (coordinating center), which repeats the same checks, to ensure that the final database contain no errors and have no missing data.

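### The named repeated-measures ANOVA uses only women with all four scores although about 30% loss is expected, and it yields no antepartum treatment estimate; a likelihood-based mixed model with entry period by time does both better

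*Protocol article*

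**What the plan says.** The Data Analysis Plan section of the protocol article fixes the method for the intervention part: "Analysis of variance for repeated measurements will be performed to compare the differences between each initial score" and the scores at T1 (end of treatment), T2 (6 months) and T3 (12 months). Bonferroni comparisons, Cohen's d per follow-up and a Reliable Change Index follow, all in SPSS 22. The section separates antenatal from postpartum women for prevalence and risk factors, but not for the treatment effect.

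The Sample Size section bases the intervention part on "detecting an effect size of medium magnitude (*d* = 0.55) at the follow-ups on the EPDS among the patients" and finds that "a sample size of 45 patients would result in a power of 0.95". It then enrols 65: "To protect against an anticipated loss to follow-up of about 30" per cent.

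On what is to be shown, hypothesis 4 takes postpartum effectiveness from a prior Italian study and adds: "we assume that intervention can be effective also with antepartum depressed women". Objective 4 under Main Objectives names both antenatal and postnatal depression.

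On delivery, Phase 4 says: "The intervention consists of group-based CBT". Groups have at least three women, and individual treatment is the fallback.

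**The concern.** Three features of the plan do not fit the method it names.

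- **Missed visits.** A woman who misses one of the four assessments contributes nothing to a classical repeated-measures ANOVA, including the scores she did give. If leaving is related to symptoms, the women who remain are a selected group and their mean change is not the mean change of those enrolled. A concrete route exists: the Follow-up section refers women still depressed after the intervention to another service. It does not say that they leave the study, but the end-of-treatment score could plausibly influence later attendance.
- **Antepartum women.** The new claim in hypothesis 4 is about pregnancy, and no planned treatment result isolates it. A pooled improvement could come mostly from postpartum women.
- **Therapy groups.** Women treated together share a therapist and a group. The named ANOVA has no term for this.

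At stake are the size of the reported effect, its standard error, and whether hypothesis 4 is tested at all.

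**Working it through.** **1. The plan's own figures.** Inputs from Sample Size: d = 0.55, alpha 0.05 (sidedness not stated), power 0.95, loss 30%. For a two-sided paired t-test the noncentrality is d√n. At n = 45 it is 0.55 × √45 = 3.69 and power is 0.950, and 45 is the smallest n that reaches 0.95. (A one-sided test would need only 38.) Enrolment: 45 / 0.70 = 64.3, so 65. Both figures reproduce. Completers expected: 65 × 0.70 = 45.5, so about 20 women are lost to the four-visit analysis and power stays at about 0.95.

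**2. Bias when loss depends on symptoms.** Assumed, because the article does not give them: EPDS SD 5 and correlation 0.5 between visits. The SD of a change is then 5 × √(2 × (1 − 0.5)) = 5, and d = 0.55 is a true change of 2.75 points at every visit. Women with a higher last score are more likely to leave, and about 45 of 65 complete. Mean simulated improvement:

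| When loss can occur | Complete-case T1 / T2 / T3 | Error against 2.75 |
|---|---|---|
| Only after T1 | 3.19 / 3.11 / 2.75 | +16% / +13% / 0% |
| Also before T1 | 2.75 / 2.71 / 2.39 | 0% / −1% / −13% |

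A likelihood model on all observed scores gave 2.71 to 2.78 throughout. The size varies with how strongly loss follows the score. Over a range of strengths, complete-case T1 ran from 2.97 to 3.21 (+8% to +17%) in the first pattern, and T3 from 2.43 to 2.61 (−12% to −5%) in the second. If all loss precedes T1, complete-case T1 falls to 1.94 to 2.39 (−29% to −13%).

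If loss is completely random, both methods are unbiased. Standard errors of the T3 change are then 0.149 SD (complete case) and 0.141 SD (likelihood), a gain of 1 − 0.141/0.149 = 5%.

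**3. Antepartum estimate.** The antepartum share is not given. Power at d = 0.55, two-sided 0.05, among 45 completers:

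| Assumed antepartum share | n | Power |
|---|---|---|
| 25% | 11 | 0.38 |
| 33% | 15 | 0.51 |
| 50% | 22 | 0.69 |
| 75% | 34 | 0.88 |

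At n = 22 the 95% interval has a half-width of about 0.44 SD.

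**4. Clustering.** Neither the ICC of the change score nor the mean group size is given. Design effect = 1 + (m − 1) × ICC, with all women assumed to be treated in groups:

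- m = 3, ICC 0.05: 1 + 2 × 0.05 = 1.10. Effective n is 45 / 1.10 = 40.9, power 0.93, true alpha of the unadjusted test 0.062.
- m = 8, ICC 0.10: 1 + 7 × 0.10 = 1.70. Effective n is 45 / 1.70 = 26.5, power 0.78, true alpha 0.133.

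The form of the group term matters. A random intercept that is the same at every visit cancels from a woman's change from baseline. In a simulation of 8 groups of 8 with a group effect arising after baseline, the true standard error of the change was 0.79. The unadjusted analysis reported 0.61, and so did a model with a random group intercept.

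**The case against.** The strongest reply is one of scope. This is a condensed article, and the analysis population, missing-visit rules, cluster terms and sensitivity analyses usually sit in a SAP that is not shown. That stands against any complaint that such details are absent. It does not answer this point, because the article names the model, the visits and the software, and exclusion of incomplete cases follows from that model.

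Other parts of the reply also stand.

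- A reader might infer that completers overstate improvement. The documents do not say when women leave, and the sign changes with timing.
- A reader might infer that about 30% of the power is thrown away. It is not: 65 was chosen to leave 45, and the precision gain under random loss is about 5%.
- A reader might set the Quality Control aim, "to ensure that the final database contain no errors and have no missing data", against the expected loss. In context it concerns checks on data that centres have collected and entered. It does not claim that visits are never missed.
- Cohen's d and the Reliable Change Index are planned for each follow-up and are not stated to need all four scores, so women with partial data may still appear there.
- A pooled analysis does serve objective 4, which names both periods. It does not serve hypothesis 4.

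**Conclusion.** The point holds as a recommended change of method. The named ANOVA excludes about 20 of 65 women and is biased if loss depends on symptoms. Under the assumed SD, correlation and fairly strong dependence on the last score, the error is about +13% to +16% at T1 and T2 when loss starts after T1, and about −13% at T3 when it can start before. The direction cannot be known from the protocol. The planned power of 0.95 is unaffected.

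Separately, no planned treatment estimate bears on hypothesis 4. Such an estimate would have power of only about 0.69 at an assumed half share of completers, so it should be read through its confidence interval.

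Ignoring therapy groups probably makes the standard errors too small. The size rests wholly on an assumed ICC and group size.

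It is tempting to conclude that switching to a mixed model cures all of this. It does not. The switch alone deals with missed visits, and only under missing at random. The antepartum estimate and the clustering each need their own term. No model replaces the control group, whose absence the article already lists as a limitation.

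**What to change.** In the Data Analysis Plan, replace the repeated-measures ANOVA by a likelihood-based linear mixed model (SPSS MIXED, the same package):

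- all enrolled women with a baseline score;
- categorical time, unstructured covariance within woman, and entry period (antenatal or postnatal) by time;
- changes at T1, T2 and T3, and the antepartum change at each, with confidence intervals;
- a therapy-group by post-baseline-time random effect, partially nested because some women are treated individually, with small-sample degrees of freedom because groups will be few;
- a sensitivity analysis under missing not at random, in which women who leave are assumed to do worse than the model predicts.

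The Quality Control sentence can stay. At most, add that it refers to data entry.

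The cost is wording and slightly more programming, with no new software or assessments; centres need to record therapy-group membership if they do not already. The main analysis will rely on missing at random, which is why the sensitivity analysis belongs with it.

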#### Phase 5: Follow-up

Changes in the patients’ clinical conditions are re-evaluated at three points of follow-up (end of intervention, 6th month and 12th month) using EPDS, PHQ-9, STAI, WHOQOL-BREF, QUITs, MINI-Plus and a clinical interview.

Mothers who are still depressed after the intervention phase are sent to a clinical psychological or psychiatric service.

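### On the listed schedule, the pre-post baseline for EPDS, PHQ-9 and STAI is the screening score that helps select the women, so part of the reported treatment effect will be regression to the mean, and T2 and T3 also reflect other care

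*Protocol article*

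**What the plan says.** All references are to the Protocol article.

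- **Screening (Phase 2).** EPDS, PHQ-9 and STAI are completed here: "Screening is performed once during the pre- or post-partum period, depending on the characteristics of each healthcare center". The next step depends on the result: "Mothers are required to complete the psychodiagnostic evaluation within one week of the date of positive screening results".
- **Diagnostic step (Phase 3).** This section opens differently: "All mothers undergo an interview with a clinical psychologist". Then, "in the case of clinician-generated diagnosis of perinatal depression and/or anxiety (according to the DSM-5 criteria), these mothers are further assessed" with the MINI-Plus, WHOQOL-BREF and QUIT. No repeat of EPDS, PHQ-9 or STAI is listed. Women found depressed and/or anxious are invited to the intervention.
- **Intervention (Phase 4).** Individual treatment is offered if a group of three cannot be formed "within a few weeks of the psychodiagnostic evaluation".
- **Follow-up (Phase 5).** EPDS, PHQ-9 and STAI are listed again at end of intervention, month 6 and month 12. "Mothers who are still depressed after the intervention phase are sent to a clinical psychological or psychiatric service".
- **Data Analysis Plan.** A repeated-measures analysis of variance will "compare the differences between each initial score obtained with the different administered questionnaires and the scores at T1 (end of treatment"), and also with T2 and T3. Cohen's d at each follow-up is called the treatment effect, and a Reliable Change Index is computed for each woman at each time.
- **Main Objectives and Study Outcomes.** "The fourth objective is to evaluate the effectiveness of a manualized psychological intervention". Depressive and anxiety symptom severity are the primary outcomes.
- **Strengths and Limitations.** The lack of a control or waiting-list group is acknowledged. The same section says that all mothers were assessed by both questionnaire and interview.

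**The concern.** A score that helped to select a woman because it was high is expected to fall when it is measured again, treated or not. EPDS covers the past 7 days, PHQ-9 the past 14 days, and the STAI state scale the current situation, so all three pick up transient states. Session 1 may come a week or two after screening for the diagnostic steps, plus the time needed to form a group. The plan tests change from this score against zero and attributes it to treatment.

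At T2 and T3 there is a second problem. Women who did not recover are referred elsewhere, and their later scores still count towards the same effect. The referral itself is not in question, only how the analysis credits it.

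At stake is the fourth objective, on the primary outcomes: a significant pre-post change could arise to an unknown degree from the choice of baseline.

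**Working it through.** **1. The plan's own figure.** The Sample Size section gives 45 patients, d = 0.55, power 0.95, alpha 0.05. A two-sided paired t-test with non-centrality 0.55 × √45 = 3.69 has power 0.950, and 45 is the smallest n that reaches 0.95. With 30% loss, 45 / 0.70 = 64.3, rounded up to 65. The figure reproduces as a test of mean change against zero, with d = mean change / SD of change. The same d is used below.

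**2. Which score is the baseline.**

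| Step | EPDS, PHQ-9, STAI | WHOQOL-BREF, QUIT |
|---|---|---|
| Phase 2, screening | yes, once | no |
| Phase 3, diagnosis | not listed | yes |
| Phase 5, T1, T2, T3 | yes | yes |

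The only listed value of the three scales before T1 is the screening score. WHOQOL-BREF and QUIT are first taken later and are not affected by selection on the screening score.

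**3. Inputs for the bias.** Share selected, p: 10-15%, borrowed from the EPDS prevalence in the Sample Size section. Test-retest correlation, r: not in the article, so 0.6-0.9 is assumed. (The 0.80 reported for the Italian EPDS is internal consistency and only a loose guide.) True treatment effect: zero. Scores: bivariate normal, in population SD units.

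**4. The score is the only selector.** With cut c = z(1-p) and λ = φ(c)/p:

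- expected fall = (1 - r)λ
- SD of change = √[1 - r² + (1 - r)²v], where v = 1 + cλ - λ²

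For p = 0.10: c = 1.282, λ = 0.1755/0.10 = 1.755, v = 0.169. At r = 0.8 the fall is 0.2 × 1.755 = 0.351, the SD of change is √(0.36 + 0.04 × 0.169) = 0.606, and d = 0.58.

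For p = 0.15: λ = 0.2332/0.15 = 1.554, v = 0.195. At r = 0.8 the fall is 0.311, the SD of change is 0.606, and d = 0.51.

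**5. A diagnosis also selects.** This was simulated (6 million). The diagnosis depends on the same true severity, with reliability 0.5 or 0.8 and error independent of both scores. The cut is 10% or 15% on both the score and the diagnosis.

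| r | Score only: d (chance of p<0.05, n = 45) | Score plus diagnosis: d (chance) |
|---|---|---|
| 0.6 | 0.76-0.86 (>99%) | 0.50-0.60 (90-97%) |
| 0.7 | 0.64-0.73 (99% or more) | 0.41-0.49 (76-90%) |
| 0.8 | 0.51-0.58 (92-97%) | 0.32-0.39 (54-72%) |
| 0.9 | 0.35-0.40 (64-75%) | 0.21-0.26 (28-40%) |

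**6. Diagnosis is the only selector, with independent error.** d = 0 and the chance is the nominal 5%.

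**7. Can a formula correct it?** Testing change against (1 - r) × (baseline mean - population mean) is right only in case 4. In case 5, with r = 0.8, a 15% cut and diagnostic reliability 0.8, it predicts a fall of 0.336 against a true 0.188, which is 79% too much. Over the whole grid it over-corrects by 55-84%.

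**8. T2 and T3.** The article gives no referral or uptake rate, so the contribution of other care cannot be computed. It does not affect T1.

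**The case against.** A reader might infer that a significant result and a medium effect are close to guaranteed with an inert treatment. The document does not support that. The screen is at most the first gate: a clinician's DSM-5 diagnosis, checked with the MINI-Plus, precedes the invitation. Phase 3 and the Strengths section even say that all mothers are interviewed; if so, and if diagnosis alone selects with independent error, this bias disappears. Entry through anxiety also weakens selection on EPDS. The Measures section reports EPDS cut-offs of 12 and 11 without adopting either, so the share selected is an assumption. This part of the objection stands, and it is why the size is given as a range that reaches down to zero.

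Two qualifications limit it. Phase 2 ties the evaluation to a positive screen, which contradicts the statement that all mothers are interviewed. The diagnosis also follows screening within a week or two, so it probably shares the woman's transient state, and fully independent error is the favourable extreme.

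A second objection is that no sentence equates the initial score with the screening score, and the timeline figure is not available. A pre-session measurement cannot be excluded, but the phases as written list none.

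Third, the missing control group is disclosed. That disclosure mentions neither regression to the mean nor care after T1, and the analysis section keeps the treatment-effect label. Nor is this a detail left to an analysis plan: the article itself fixes the comparison, the time points and the label.

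**Conclusion.** The point holds in a limited form. On the listed schedule, the baseline for the primary outcomes is a score that helps select the women, so part of the fall to T1 is likely to be regression to the mean, reported as treatment effect. With zero treatment effect, d is about 0.35-0.86 if the score is the only selector. It is about 0.2-0.6 if an independent diagnosis also selects, with a chance of p<0.05 at n = 45 from just under 30% to 97%. It is about 0 if diagnosis with independent error is the only selector. The planned effect of 0.55 lies inside the first two ranges. These figures rest on normal scores, an assumed r of 0.6-0.9, and 10-15% taken as the share selected.

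T2 and T3 are further mixed with other care, by an amount that cannot be computed. The sample size arithmetic is not in error. The missing control group cannot now be repaired, but the choice of baseline can be, cheaply.

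**What to change.** (a) Give EPDS, PHQ-9 and STAI again after the diagnostic evaluation and immediately before session 1. Use that score as T0 for the analysis of variance, Cohen's d and the Reliable Change Index.

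(b) For women already treated, report a sensitivity analysis of expected regression over a range of r and of selection models (screen only, screen plus diagnosis). Do not test against the single-gate formula in step 7.

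(c) Make T1 the main time point, record other care received after T1, and report T2 and T3 also with referred women counted as non-responders.

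(d) Describe the result as uncontrolled pre-post change rather than treatment effect or effectiveness. This is still needed after (a), because natural recovery after T0 remains in the change score.

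(e) Reconcile the positive-screen gate in Phase 2 with the statements in Phase 3 and in Strengths and Limitations that all mothers are interviewed or assessed.

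The cost is one more short questionnaire pack per woman, some extra analysis, and probably a smaller reported effect. No change to care is involved.
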